In 2011 and 2012, we conducted a pilot trial of the Respecting the Circle of Life (RCL) peer-group component (8 lessons taught during summer basketball camp) without the additional youth-parent lesson [18, 19]. Immediately post-camp, RCL participants had significantly greater condom use self-efficacy, intention to use condoms at next sex, HIV/STI prevention and transmission knowledge, partner negotiation skills related to alcohol and drug use during sex, and belief in the protective effects of condoms and abstinence [19]. RCL participants were also more likely to talk with a family member or other adult about HIV/AIDS [19]. Regarding the theoretical constructs underpinning the RCL intervention, all positive protective factors, including self-efficacy (ability to engage in behaviors to reduce risk for STIs/HIV), response efficacy (ability of the protective behavior to actually reduce risk, i.e., efficacy of condoms to prevent infection and pregnancy) and response cost (negative impacts of engaging in the protective behavior), were significantly improved among RCL participants [19].

Improvements in condom use self-efficacy, HIV/STI prevention and transmission knowledge, belief in the protective effects of condoms, talking with a family member or other adult about HIV/AIDS, and response efficacy were sustained at 6 months follow-up [19]. Changes in condom use self-efficacy and response efficacy were sustained through 12 months [19]. All other impacts attenuated at 12 months, which is consistent with previous trials of the FOY peer-group component [14–16, 20]. In an effort to extend intervention impacts past 6 months, previous research groups added the ImPACT youth-parent component and found both existing and additional intervention impacts (including substance use initiation and subsequent substance use) sustained through 24 months [21, 22].

Thus, the aim of this trial is to evaluate the effect of the RCL intervention, including both peer-group (8 lessons) and youth-parent components (1 lesson), on knowledge, attitudes and behaviors associated with unprotected sex and unintended pregnancy among an exclusive sample of AI adolescents. Utilizing a randomized controlled trial (RCT) design, we will test whether the RCL intervention affects well-established intermediate outcomes and risky sexual behaviors that predict a long-term impact on the incidence of teen pregnancy [23].

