### Intervention: Respecting the Circle of Life: Mind, Body and Spirit (RCL)

RCL consists of a peer-group (adapted FOY lessons) and a youth-parent component (adapted ImPACT lesson). The peer-group component consists of eight lessons, each lasting ~120 min, delivered by two trained AI community health workers to self-selected same-sex peer groups of 8–12 AI youth. The eight lessons are delivered once per day during the 8-day summer basketball camp. The youth-parent component is one educational lesson lasting 90–120 min delivered within 3 months after the end of camp, to the youth and parent/trusted adult, together with an AI community health worker.

RCL focuses on: (1) extrinsic rewards, by teaching decision-making related to communication and negotiation skills around sex, as well as information regarding birth control and condom use, and (2) intrinsic rewards, by emphasizing values clarification and goal setting. Peer-group instruction incorporates discussion, lectures, games, role playing and storytelling. RCL content covers: (1) reproductive and sexual health education; (2) instruction about condom use, contraception, STIs, safe sex practices and pregnancy prevention; (3) partner communication and negotiation skills for sex and substance use; (4) peer refusal for unwanted sex and substance use; (5) peer norms related to delaying sexual initiation; and (6) linkages to community resources. Youth-parent instruction incorporates a DVD and skills-based activities focused on: (1) information about sexual and reproductive health; (2) promoting family values pertaining to sex and substance use; (2) techniques for youth-parent communication and effective parental monitoring; (3) how to support youth condom and contraceptive use; and﻿ (4) decision-making pertaining to sex.

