### Control Program

The control program is identical in structure and delivery mode to RCL and consists of peer-group and youth-parent components. The control program does not include any content pertaining to sexual and reproductive health, to ensure no overlap. Lesson content includes: (1) knowledge about food labels and general nutrition; (2) information about different types of physical activity; (3) activities to encourage youth to eat healthy; and (4) relaxation techniques. Implementing a control program identical in structure but different in content will ensure observed impacts on key outcomes can be attributed to the content of the RCL program.

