### Randomization

Participants will be individually randomized to receive the intervention or control program. Participants will be assigned to either program through a stratified block randomization sequence using Stata 14 [24] to ensure a 1:1 allocation of study conditions occurs within each gender and age sub-group (11–12, 13–15 and 16–19). Since both the RCL and control program include a youth-parent component, siblings will be randomized to the same group.

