This sample size will also be able to detect meaningful differences between the intervention and control groups with at least 80% power, given the assumptions listed above: 6.7% between-group difference in reproductive/sexual health knowledge score [estimating a mean score (SD) of 76% (16%) in the control group] and 20.5% between-group difference in intention to use a condom at next sex (estimating 55% in the control group).

Study hypotheses will be initially tested under an “intent-to-treat” model in which data are analyzed according to randomization assignment. We will then conduct “completer analyses” on those subjects finishing at least two-thirds of the 9 intervention sessions. Intervention impact will be evaluated by comparing primary study outcomes between intervention and control groups across the three time points: baseline, 3 and 9 months post-intervention. Initially, summary scores of outcomes will be stratified by participation in the intervention versus control groups and by time point and compared using chi-square tests (for binary or categorical outcomes), t-tests and analysis of variance (for continuous outcomes). The equivalence of the two study groups at baseline will be compared across a range of background variables. Generalized linear mixed effects models (GLMMs) accounting for within-group correlation across longitudinal data will then be applied.

Outcomes will be modeled as a function of group assignment and time since intervention. The association between outcomes and time will be explored visually using scatterplots and lowess smoothers. Restricted cubic splines will be added to reflect deviations from linearity. GLMM with random intercepts for peer group and study participant will be used to account for the hierarchical structure of the data: peer group, participants nested within peer group and assessments nested within study participants. If siblings enter the study together during the same wave, they will be randomized to the same study group (intervention or control) to limit contamination. In this case, analyses will be adjusted to take into account intra-sibling correlation as well. Missing data will be handled as follows: (1) document reason(s) for missing data to inform model development; (2) assess treatment dropouts to do intent-to-treat analysis; (3) conduct sensitivity analysis to compare inferences that are based on different plausible reasons for missingness [32, 33].

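### The completer analysis compares youths selected by attendance after randomisation, and its 6-of-9 threshold can be met from camp lessons alone, so it is neither a randomised comparison nor an estimate for the full two-component programme

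*Protocol article*

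**What the plan says.** The section on sample size and statistical analysis puts the randomised comparison first: "Study hypotheses will be initially tested under an “intent-to-treat” model in which data are analyzed according to randomization assignment". Completer analyses follow, on "those subjects finishing at least two-thirds of the 9 intervention sessions". The rule is a count of sessions, and no component is compulsory.

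The intervention section gives the make-up of the nine: "The peer-group component consists of eight lessons", and "The youth-parent component is one educational lesson lasting 90–120 min delivered within 3 months after the end of camp". The Background states that the aim is to evaluate the programme "including both peer-group (8 lessons) and youth-parent components (1 lesson"), and explains why the ninth session is there: "In an effort to extend intervention impacts past 6 months, previous research groups added the ImPACT youth-parent component". The pilot delivered the camp lessons without it.

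On design, "Participants will be individually randomized to receive the intervention or control program", with siblings kept together. The section on data collection time points says that participants cannot be blinded. The control section says: "The control program is identical in structure and delivery mode to RCL". A session count can therefore be applied in both arms, although the article does not say that it will be.

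**The concern.** Two features of the completer set limit what it can show.

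First, the set is formed by behaviour after randomisation. Youths know whether they are in a sexual-health or a nutrition programme, and those who keep attending one may differ from those who keep attending the other. Any such difference enters the completer comparison as if it were a programme effect.

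Second, the label suggests receipt of the programme, but the count treats the youth-parent lesson as interchangeable with any camp lesson. That lesson is delivered separately after camp and needs a second person, so it is plausibly the session most often missed. The completer group may therefore include many youths whose exposure was the camp-only programme of the pilot.

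At stake is the reading of the only as-received analysis that the article names. The intent-to-treat result is not affected.

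**Working it through.** **Threshold.** 9 × 2/3 = 6 sessions. The camp offers 8, so 6 of 8 camp lessons qualify with no youth-parent lesson.

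**Attendance patterns that qualify.**
- Without the youth-parent lesson (at least 6 of 8 camp lessons): C(8,6) + C(8,7) + C(8,8) = 28 + 8 + 1 = 37.
- With it (at least 5 of 8): 56 + 28 + 8 + 1 = 93.
- Total 130, of which 37 lack the lesson and 1 is full attendance.

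Pattern counts show what the rule permits, not how often it will happen.

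**Possible share of completers without the lesson.** The article gives no attendance rates, so these are assumptions: independent attendance, camp attendance c per lesson, youth-parent attendance p, and X ~ Binomial(8, c).

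Share = (1 − p)·P(X ≥ 6) / [p·P(X ≥ 5) + (1 − p)·P(X ≥ 6)]

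For c = 0.8, P(X ≥ 6) = 0.797 and P(X ≥ 5) = 0.944. With p = 0.5 the share is 0.398 / (0.472 + 0.398) = 46%.

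| Youth-parent attendance p | c = 0.8 | c = 0.9 |
|---|---|---|
| 0.9 | 9% | 10% |
| 0.7 | 27% | 29% |
| 0.5 | 46% | 49% |

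**Possible selection bias with no true effect.** Assume that the same count is applied in both arms, that attendance follows a normal trait correlated r with the outcome, and that completers are the top fraction q. Their mean outcome is then shifted by r·φ(c_q)/q SD, where c_q is the cut-off leaving a fraction q above it. The spurious difference is the gap between the two arms' shifts.

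- q = 0.85: φ/q = 0.274. q = 0.70: φ/q = 0.497. The gap is 0.222, so r = 0.2, 0.3, 0.5 gives 0.044, 0.067, 0.111 SD.
- q = 0.80 versus 0.60: the gap is 0.294, giving 0.059, 0.088, 0.147 SD.
- Equal q and equal r: the gap is 0.
- Equal q = 0.80 but r = 0.3 in one arm and 0.1 in the other: 0.350 × 0.2 = 0.07 SD.

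The plan's target is 0.47 points with SD 1.0, so 0.044 to 0.111 is 9% to 24% of it. The arm with lower completion is favoured when r is positive. The article does not indicate which arm that would be.

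**Complier-average estimate under two definitions of compliance.** Assume that 90% of the intervention arm receive a sufficient camp dose with effect 0.47, and that the youth-parent lesson adds nothing. The intent-to-treat effect is 0.90 × 0.47 = 0.423.

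- If the 90% are the compliers: 0.423 / 0.90 = 0.47, the true value.
- If compliance also requires the youth-parent lesson and 60% to 75% then qualify: 0.423 / 0.75 = 0.56 to 0.423 / 0.60 = 0.71, which is 20% to 50% too large.

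**The case against.** The strongest reply is that this analysis is already subordinate. Intent-to-treat is tested first, the sample size and the 0.0125 level do not rest on the completer set, and loss of randomisation is true of every completer analysis. A session count is a legitimate dose threshold, and the article may leave estimators for a supplementary analysis to a fuller document. All of this stands and keeps the weight modest. It does not change the fact that the analysis, as stated, is restricted to youths selected on attendance.

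The bias may also be small. The control programme matches in structure, so completion could be similar in both arms. The primary outcomes are framed as change from baseline, so stable differences between attenders and non-attenders are partly removed and the relevant r is with change. That stands too: bias is possible, not shown.

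Some stronger readings are tempting but not supported:
- A reader might infer that the article presents the completer result as the whole-programme effect. It does not say so. The caution concerns how the label may be read.
- A reader might fault this analysis for not showing whether the youth-parent lesson sustains effects to 9 months. No analysis of this trial could show that by randomisation. There is no camp-only intervention arm, and the stated aim is the combined programme.
- A reader might conclude that completers should be redefined to require the youth-parent lesson. Combined with a complier-average estimate, that assumes camp-only attenders gain nothing. The Background contradicts this: the camp-only pilot improved several outcomes, with condom use self-efficacy sustained to 12 months.

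**Conclusion.** The point holds with modest weight. The completer comparison does not keep the randomised comparison, and its 6-of-9 threshold can be met without the youth-parent lesson. It should not be read as an unbiased effect of attendance or as the effect of the two-component programme.

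The arithmetic of the threshold is certain. The size of the bias is not known: zero with like completion and selection in both arms, and about 0.04 to 0.11 SD under the assumed 85% versus 70% completion and r of 0.2 to 0.5. The assumed 80% versus 60% gives 0.06 to 0.15 SD. No completion rate or correlation appears in the article, so these figures illustrate a risk and do not estimate it. The trial's main conclusions are not threatened as long as they rest on intent-to-treat.

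**What to change.** 1. State that conclusions rest on the intent-to-treat analysis and that the as-received analysis is supportive.
2. Keep the stated threshold of at least 6 of 9 sessions. In place of the direct completer comparison, or beside it, estimate a complier-average causal effect with randomised arm as the instrument and the same covariates as the primary model.
3. Do not make the youth-parent lesson a condition of compliance.
4. Report completion by arm and by component, with camp lessons and the youth-parent lesson shown separately, so that readers can see what completers received.
5. Repeat the estimate with a lower threshold, for example any attendance, because the complier-average estimate assumes that attending fewer than 6 sessions has no effect.

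The cost is a change of wording and one additional model with a sensitivity run, using session attendance that the completer rule already requires. The sample size does not change. The downside is a wider interval than the direct comparison gives, and reliance on the assumption that item 5 checks.

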### Participants

Youth participants will be of AI ethnicity, ages 11 to 19 and have primary residence on or near the participating tribal reservation community. Parent/trusted adult participants will be chosen by the youth and be the parent/legal guardian of the participating youth or another family member or trusted adult over the age of 18. If the youth choses an adult who is not the legal guardian, the adult must be approved by the legal guardian. Participants who are unable to fully participate in the evaluation assessments or intervention components will be excluded (see Table 1 for Inclusion and Exclusion criteria). All participants will complete informed consent to participate; youth under age 18 will have parent/guardian consent.

**Table 1 Tab1:** Inclusion and exclusion criteria

Inclusion criteria		
	Youth	-Self-identified American Indian -11-19 years old -Primary residence on or near the reservation -Written informed consent (parent/guardian consent if 11–17 years old)
	Parent/trusted adult	-Parent, legal guardian or trusted adult -18 years old or older -Primary residence on or near the reservation -Written informed consent
Exclusion criteria		
	Youth	-Unwilling to be randomized -Unable to complete intervention because of cognitive limitations -Unable to complete evaluation (i.e., planned move, residential treatment, etc.)
	Parent/trusted adult	-Unwilling to be randomized -Unable to complete intervention because of cognitive limitations -Unable to complete evaluation (i.e., planned move, residential treatment, etc.)

We will use non-probability sampling to recruit participants through public postings in community gathering spots (i.e., supermarket, daycares, fitness center, etc.), through public service announcements on the local radio, by print advertising in the local newspaper, during public gatherings (i.e., health fairs, parades, etc.) and through local schools. We will recruit three cohorts of participants and host three summer basketball camps (2016, 2017 and 2018).

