### Sample Size Calculation and Statistical Analysis

Our goal is to recruit 567 youth (and their parent/trusted adult) balanced within two age groups (11–12, 13–15 and 16–19), for a total of 1134 participants (567 youth and 567 parents/trusted adults). We expect a maximum attrition rate of 25%, based on past rates in similar evaluations [18, 19, 29, 30].

Sample size estimates were based on the variables of condom use self-efficacy and sexual initiation because these confirmatory research questions apply to all study participants, and prior studies have shown them to be associated with reductions in risky sexual behavior, teen pregnancy and STI incidence [23]. We hypothesize that the RCL intervention will increase condom use self-efficacy in the intervention group compared to the control group and that the intervention group will have a lower proportion of participants who initiate sex, compared to controls, at study end line.

The condom use self-efficacy scale ranges from 1–5. Our pilot trial [18] provided data on the condom use self-efficacy score among the control group (mean = 2.6, SD = 1.0), degree of intra-team correlation (“k” = 0.12) and potential loss to follow-up over 9 months (20% average reduction in team size, i.e., from 9 down to 7.2 youths). Although this trial will utilize individual randomization, the intervention will be carried out with teams of 8–12 participants each, which will require accounting for intra-team correlation.

We will use the average of two follow-up measures of condom use self-efficacy per participant (intra-measure correlation = 0.7) to reduce error in outcome measurement [31]. To achieve 90% power to detect a theoretically meaningful between-group difference of 0.47 points on this scale over 9 months post-intervention, ~32 teams per study arm will be required. Thus, we will enroll and randomize a total of *n* = 284 participants per study arm (32 teams/arm *9 participants/team), for a total sample size of *n* = 567 participants. We have reduced the significance level used in sample size calculations to 0.0125 to account for multiplicity corrections during analyses. This same sample size will be sufficient to detect a 19.7% between-group difference, with 80% power and 0.0125 significance level, in the percent of participants who report ever having had sex. This estimate is conservative based on our past retention rates and accounts for up to 25% loss to follow-up, while adjusting for the intra-team correlation.

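### Gender and age group stratify the randomisation but are absent from the stated outcome model; adding them costs nothing and recovers some power if arms are compared on follow-up values

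*Protocol article*

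**What the plan says.** The Randomization section of the protocol article uses stratified blocks "to ensure a 1:1 allocation of study conditions occurs within each gender and age sub-group", with age bands 11–12, 13–15 and 16–19. That makes six strata.

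The section Sample Size Calculation and Statistical Analysis gives the fixed part of the model: "Outcomes will be modeled as a function of group assignment and time since intervention". It allows splines for time and an adjustment for sibling correlation, and gives the random part: "GLMM with random intercepts for peer group and study participant will be used to account for the hierarchical structure of the data". Neither gender nor age group appears. No sentence rules covariates out.

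The same section describes the evaluation as "comparing primary study outcomes between intervention and control groups across the three time points: baseline, 3 and 9 months post-intervention". It sizes the trial, however, on the average of two follow-up measures of self-efficacy and on the proportion initiating sex at end line. It does not state a group-by-time interaction.

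Two design features bear on the point. The programme is delivered to "self-selected same-sex peer groups of 8–12 AI youth", so gender lies entirely between peer groups. Recruitment runs in three yearly cohorts, but cohort is not named as a randomisation stratum.

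**The concern.** Stratifying on a prognostic factor makes the arms more alike than chance would, so the estimated arm difference varies less from trial to trial. A model that omits the factor does not see this. It leaves the factor's variance in the error terms and reports a standard error that is too wide.

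Here gender, and age to whatever extent self-selected peer groups sort by age, would sit in the peer-group intercept, the component that weighs most on the arm comparison.

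Age is the factor with some support in the document. The Background reports that 69% of American Indian adolescents have ever had sex and 11% did so before age 13, and this trial enrols ages 11–19. Precision is also limited: "We have reduced the significance level used in sample size calculations to 0.0125 to account for multiplicity corrections during analyses", and the detectable difference for ever having had sex is 19.7 points.

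**Working it through.** **1. The plan's own figure.** Inputs from the sample-size section: significance level 0.0125 (two-sided reproduces the result; sidedness is not stated), power 0.90, SD 1.0, control mean 2.6, difference 0.47 (intervention mean 3.07), team size after loss m = 7.2, k = 0.12, correlation of the two follow-ups 0.7. Averaging two measures gives a variance factor of (1 + 0.7)/2 = 0.85.

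With k read as a between-team coefficient of variation:

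teams per arm = 1 + (2.498 + 1.282)² × [2 × 0.85/7.2 + 0.12² × (2.6² + 3.07²)]/0.47²
= 1 + 14.28 × (0.2361 + 0.2331)/0.2209 = 31.3, so 32.

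The standard error at 32 teams is √(0.4692/31) = 0.1230, and power is Φ(0.47/0.1230 − 2.498) = 0.907. Reading k as an intraclass correlation gives 26.6 teams with averaging and 31.3 without. No reading uses a covariate, so the planned size does not depend on adjustment.

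**2. Simple calculation without clustering.** R² is the assumed share of outcome variance explained by the strata. Under stratified balance, the estimator's actual standard error is √(1 − R²) times the one the unadjusted model reports. For a nominal 80% test (2.498 + 0.842 = 3.340):

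- Unadjusted power = Φ(0.842/√(1 − R²))
- Adjusted power = Φ(3.340/√(1 − R²) − 2.498)
- Unadjusted true size = 2 × [1 − Φ(2.498/√(1 − R²))]

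| R² | Unadjusted power | Adjusted power | Gain (points) | Unadjusted size |
|---|---|---|---|---|
| 0.1 | 0.813 | 0.847 | 3.4 | 0.0085 |
| 0.2 | 0.827 | 0.892 | 6.5 | 0.0052 |

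**3. Self-efficacy on the plan's inputs.** Multiplying the within-team term 0.2361 by (1 − R²) gives a standard error at 32 teams of 0.1199 for R² = 0.1 and 0.1167 for R² = 0.2. Power is then 0.923 and 0.937, against a planned 0.907. The 0.907 takes the reported and actual standard errors as equal. If balance already lowers the actual one, the unadjusted test has power Φ((0.47 − 2.498 × 0.1230)/0.1199) = 0.913 or, with 0.1167, 0.918. The net gain is then 1 to 2 points.

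**4. Ever having had sex.** With three equal age bands, R² = variance of the band rates/[p(1 − p)], and the detectable difference is 19.7 × √(1 − R²). The band rates are assumed.

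| Rates, youngest to oldest | R² | Detectable difference |
|---|---|---|
| 11/40/69% | 0.23 | 17.2 points |
| 5/17/45% | 0.16 | 18.0 points |
| 10/20/38% | 0.08 | 18.9 points |

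The baseline of 19.7 likewise takes reported and actual standard errors as equal.

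**5. Which contrast matters.** A simulation used 64 same-sex teams of 7, with 400 runs per setting and stratum effects constant over time. It gave these average model standard errors without and with strata:

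| Contrast | R² | Age-banded teams | Mixed-age teams |
|---|---|---|---|
| Follow-up values | 0.1 | 0.139 vs 0.112 | 0.120 vs 0.111 |
| Follow-up values | 0.3 | 0.171 vs 0.099 | 0.125 vs 0.099 |
| Baseline as covariate | 0.1 | 0.101 vs 0.098 | 0.098 vs 0.097 |
| Baseline as covariate | 0.3 | 0.096 vs 0.086 | 0.089 vs 0.086 |
| Change from baseline | 0.1 | 0.102 vs 0.102 | 0.101 vs 0.101 |

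In age-banded teams at R² = 0.1 (follow-up contrast), the actual spread of the estimate was 0.112 with or without strata. The harm there is an overstated standard error, not a noisier estimate.

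**The case against.** The strongest defence is that the primary outcomes are defined as changes from baseline, and that the comparison includes the baseline assessment. Under a change contrast, time-constant stratum effects cancel and adding strata gains nothing. This stands as far as it goes. But the model text states no group-by-time contrast, the sample size rests on follow-up values, and initiation over follow-up may differ by age, in which case the effects are not constant.

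A second defence is that a covariate list belongs in the analysis plan. The article, however, sets out its model in some detail (splines, nesting, siblings), and that stated model does not match the design. It would be too much to infer that covariates are excluded; nothing says so.

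Several stronger readings are tempting but unsupported:

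- **A gain from 80% to 89% at R² = 0.2 (85% at 0.1).** This sets adjusted power against a nominal 80% that assumes the reported standard error is right. If the unadjusted test is conservative, it already has 82.7% (81.3%).
- **Camp year as a stratum.** Balance within year is an inference, not a stated feature.
- **All the factors as strongly prognostic.** Only age, for initiation, has support. Nothing is given for gender or camp year.
- **Age sorted between teams.** Peer groups are same-sex and self-selected, not age-banded by rule.
- **A diluted arm effect in the logistic models.** The planned participant and team intercepts largely absorb omitted time-constant covariates, so the dilution known from ordinary logistic regression does not carry over directly.

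**Conclusion.** The point holds as a matter of efficiency and test calibration. The stated model omits the two factors used to stratify randomisation. On a follow-up contrast this makes standard errors too wide and tests conservative; on a change-from-baseline contrast the loss is small or nil.

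For assumed R² between 0.1 and 0.2, the gain from adjustment is about 3 to 7 power points in the simple calculation and smaller for self-efficacy on the plan's inputs. Every R² and every age-band rate is an assumption, and the simulated results also depend on how peer groups form.

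A reader might infer that the trial is underpowered or its result biased. Neither follows: the planned size reproduces with no covariate, and conservative tests do not inflate false positives. This is a worthwhile, essentially free improvement, not a threat to validity.

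**What to change.** Add gender and randomisation age group as fixed effects in the primary mixed model for all four primary outcomes, and make that the primary analysis. Cohort (camp year) may be added as an optional further covariate, since it is not a stated stratum. State explicitly which group contrast at 9 months is the primary effect, and whether baseline enters as a repeated outcome or as a covariate.

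The cost is a sentence or two in the analysis plan. Gender and age are already recorded for randomisation. The fixed effects use three degrees of freedom (one for gender, two for age group), or five with cohort. Sample size and data collection are unchanged.
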